#### Data Analysis

Data related to the analysis of objective 1, focusing on clinical effectiveness, will be compared between both interventions. Primary and secondary outcomes will be compared between the 2 interventions, using one as the active control for the other. First, propensity score matching will be used to identify a subset of participants who will comprise the active control group that is equivalent to the intervention group on background variables (sociodemographic variables, illness duration, medication dosage, length and nature of prior treatment as well as subjective reports of cognitive capacity and cognitive biases). Then, Z-standardized outcome data will be compared between the groups with generalized linear mixed effect modeling techniques using R software. Factors of interest will include fixed time (pre, post, and follow-up), fixed treatment (ABCR and MCT), fixed time and treatment interaction (time*treatment), random site (CIUSSS de l’Ouest-de l’Ile de Montréal, the Royal’s Institute in Ottawa, Kingston Health Sciences Centre, Ontario Shores Centre for Mental Health Sciences in Toronto, and Vancouver Coastal Health), random intercepts (participants’ ID), and random slopes (participant*time). Age, illness duration, medication dosage, length, and nature of prior psychological treatment will also be included as fixed covariates. This procedure will be done twice, with the active control group subset using propensity score matching. This approach ensures that participants are not counted twice and is an integral part of the propensity score matching procedure. Statistically, performing the procedure twice helps to validate the robustness of the matching process without introducing bias, as each participant is only included once in each comparison. Specifically, the procedure will be as follows: (1) ABCR as the intervention and MCT as the active control and (2) MCT as the intervention and ABCR as the active control. Missing data pattern will be assessed for whether it is missing completely at random, missing at random, or not at random [73]. If data are missing at random, multiple imputation will be applied [74]; if data are missing not at random, then the robustness of the primary analyses will be evaluated through sensitivity analyses.

Analyses for all implementation objectives will be executed using descriptive statistics for quantitative data and thematic analysis for qualitative data, following Braun and Clarke’s [75] interpretive descriptive approach. This method emphasizes the researcher’s active role in the analytical process, allowing for a nuanced understanding of themes such as facilitators and barriers to implementation, identified from CFIR semistructured interviews. Investigator triangulation will be used, with 3 independent raters conducting iterative qualitative analyses until a consensus (≥80%) is reached. A convergent quantitative-qualitative mixed methods design [76] will facilitate a comprehensive comparison of results from quantitative and qualitative analyses, aiming to develop a holistic understanding of factors influencing implementation. Side-by-side comparison tables will support this analytical process and engage implementation teams in interpretation. To ensure reflexivity, member checks will be conducted with participants to validate findings, ensuring that their perspectives and interpretations are accurately represented and that any potential biases in the researcher’s analysis are addressed. This methodological framework is designed to uphold rigorous standards in qualitative research while ensuring that the findings are credible, dependable, and relevant to broader contexts. All qualitative analyses will be done using NVivo (version 15; Lumivero).

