## Methods

### Study Design

A hybrid effectiveness-implementation trial [32-34] relying on digital technology will be used. The effectiveness component involves assessing the outcomes of these interventions, while the implementation component focuses on conducting the research in a way that emulates the naturalistic clinical setting. This design is ideal for transferring evidence-based behavioral interventions into real care environments [32-35], as it confirms clinical effectiveness while targeting necessary procedures to deliver and sustain such interventions in real-world care settings. A nonrandomized concurrent controlled design will be used to assess clinical effectiveness where one intervention acts as the active control for the other. The nonrandomized concurrent controlled design was selected, as it eases access to the preferred intervention by service users, overcoming the challenges of randomizing participants in real care settings and facilitating recruitment.

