### Selection Criteria

Inclusion criteria include 18 years of age or older; diagnosis of affective or nonaffective psychosis or related disorder; followed and treated by a clinician at one of the services mentioned earlier; considered symptomatically stable and capable of using the digital platforms and participating in intervention groups, as judged by their primary clinicians; access to a private space to ensure group confidentiality; and provision of emergency contact and consent to allow researchers to contact their clinician or emergency services in the event of an emergency during study procedures. Most criteria are present for the safety of the group and participants. Exclusion criteria include intellectual disability, hospitalization at the time of recruitment, inability to speak or read English or French, and high suicide risk as per evaluation. We will recruit 4-6 mental health practitioners per site who will complete training on the E-Cog training platform to deliver the 2 cognitive health interventions. Practitioners will be eligible if they have a background in psychology, social work, nursing, or any other health-related training.

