### Recruitment

Recruitment for this study uses a multimodal communication strategy designed to effectively reach potential participants. This strategy includes displaying informational flyers on hospital television screens, distributing email newsletters to health care employees, and presenting intervention details to case managers to facilitate referrals. Additionally, recruitment materials will be posted in clinic waiting rooms. n example of the recruitment pamphlet is provided in Multimedia Appendix 1. Health care team members can refer eligible participants or obtain consent for the research team to make direct contact. Participants are permitted to be engaged in other psychological or psychosocial interventions while participating in our study. Data on whether they are currently receiving other interventions will be collected.

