### Cognitive Health Interventions

Interventions will be delivered through a secure videoconference platform. Network-connected tablets will be provided as necessary for the trial duration. ABCR [27,64] sessions consist of computer-based cognitive training activities (Brain Training Pro; 60%), teaching of problem-solving strategies (20%), and transfer activities (20%). Transfer activities include discussing and role-playing how cognitive skills are applied in everyday life and teaching potential strategies for overcoming cognitive challenges. ABCR targets include processing speed, attention, memory, executive functions, and social cognition, which are all commonly impaired in psychosis [12]. ABCR will be delivered in 16 sessions lasting 1.5 hours each over an 8-week period. MCT targets cognitive biases and errors in judgment underlying delusions using the theoretical foundations of cognitive behavioral therapy [65]. Sessions consist of discussions and activities aimed at increasing participants’ awareness of distortions and expanding their current problem-solving strategies. MCT will be delivered in 12 sessions lasting 45-60 minutes each over 6 weeks.

Both interventions will be offered at all sites. Depending on the site, interventions will either be offered concurrently or in sequence. Intervention group allocation follows a personalized, participant-centered approach. Potential participants will meet individually with the research coordinator at their site, who will provide a comprehensive overview of both interventions. Together, they will collaboratively determine which intervention best aligns with the participant’s personal goals and preferences. To maximize participant benefit and engagement, individuals will have the opportunity to complete the alternative intervention after finishing their initial chosen intervention. This flexible approach ensures that participants can potentially benefit from both interventions.

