Some limitations of our study include the nonrandomized concurrent controlled design, which raises concerns about potential group differences. However, we will address this by statistically controlling for measurable background characteristics. Second, although we aim to engage a broader population by providing services using a digital format, we acknowledge that there could be variability to technology access. We have planned to provide tablets and internet to service users without access to technology. For service users or health care providers unfamiliar with technology, we will also offer orientation sessions to help them become comfortable with the digital format. Next, the recruitment of therapists within a research setting may not reflect therapists involved in nonresearch settings. In addition, although we have taken great care in selecting instruments that have been validated in our population and available in both English and French, some limitations may still exist with the instruments chosen. For instance, ceiling effects have been observed in the Cambridge Neuropsychological Test Automated Battery cognitive test. Finally, there may exist differences across 5 sites in training experiences and implementation fidelity. We plan to attend to this by standardizing training and fidelity checks conducted across all sites.

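### Participants choose their intervention, but the stated matching list and outcome model omit baseline symptoms, diagnosis, motivation, concurrent therapy and enrolment period, and handle site and objective baseline tests only in part

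*Protocol article*

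**What the plan says.** Allocation is by choice. Under Cognitive Health Interventions, "Intervention group allocation follows a personalized, participant-centered approach": participant and coordinator "collaboratively determine which intervention best aligns with the participant’s personal goals and preferences". The same section adds that "Depending on the site, interventions will either be offered concurrently or in sequence". Study Design describes the comparison this way: "A nonrandomized concurrent controlled design will be used to assess clinical effectiveness where one intervention acts as the active control for the other".

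The adjustment is set out under Data Analysis. Matching is to produce a control group "equivalent to the intervention group on background variables (sociodemographic variables, illness duration, medication dosage, length and nature of prior treatment", and self-reported cognitive capacity and cognitive biases complete the list. The outcome model then has fixed time (pre, post, follow-up), treatment and their interaction, a random site effect, and participant random intercepts and slopes. Its fixed covariates are age, illness duration, medication dosage, and length and nature of prior psychological treatment. Measures gives the same matching variables, but as examples.

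Two further sources of difference are acknowledged elsewhere. Eligibility covers "diagnosis of affective or nonaffective psychosis or related disorder", and other psychosocial treatment is permitted: "Data on whether they are currently receiving other interventions will be collected". Strengths and Limitations grants that groups may differ without randomization and continues: "However, we will address this by statistically controlling for measurable background characteristics".

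**The concern.** With self-selected groups, the time-by-treatment contrast can be read as a treatment comparison only if whatever drives both choice and change is balanced or modelled. MCT is described as targeting the biases that underlie delusions, so symptom severity is a plausible driver of choice. Diagnosis, motivation and other current therapy are plausible drivers as well. Where the two interventions run in sequence, what is on offer may also depend on when a person enrols.

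The stated matching list contains none of these. Symptoms and motivation are measured before the intervention (Table 1) and concurrent therapy is recorded, so the gap is avoidable. Bias of this kind does not shrink as the sample grows, and it matters most for the smaller planning effect (MCT, g=0.27).

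**Working it through.** **Step 1. Set the variables beside the plan.**

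| Variable | Available | In matching list (Data Analysis) | In outcome model |
|---|---|---|---|
| PANSS-6, BNSS, PSYRATS at baseline | Yes, Table 1 | No | No (only as outcomes in their own right) |
| Affective vs nonaffective diagnosis | Diagnosis is an entry criterion | No | No |
| Motivation for intervention | Yes, Table 1 | No | No |
| Concurrent therapy | Yes, Recruitment | No | No |
| Enrolment period | Assumed known from study records | No | No |
| Site | Known | No | Random effect only |
| Objective tests at baseline (CANTAB, Logical Memory, disconfirmatory evidence, Beads) | Yes, Table 1 | No | As the pre level of the outcome only |
| Self-reported cognition and biases | Yes, Table 1 | Yes | As the pre level when they are the outcome |

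Five items appear in neither place, and two are handled in part.

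**Step 2. What the partial handling achieves.** Random slopes are named for participants only, so site is read as an intercept. Take five equal sites with ABCR shares of 0.20, 0.35, 0.50, 0.65 and 0.80 and no true treatment effect (all assumed).

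- *Sites differ in level only.* Simulated bias in time-by-treatment is -0.01, in effect nil.
- *Sites differ in change*, by -0.4, -0.2, 0, 0.2 and 0.4 SD. Expected change is (0.20×(-0.4) + 0.35×(-0.2) + 0.65×0.2 + 0.80×0.4)/2.5 = 0.30/2.5 = 0.12 among ABCR participants and, by symmetry, -0.12 among MCT participants. The bias is 0.24 SD. Simulation over 25 data sets gave 0.21, and -0.03 once change was adjusted for site and symptoms; the distance from 0.24 and from 0 is simulation noise.
- *Does the random site intercept help?* In one simulated data set with site differences in change, a mixed model with site and participant intercepts returned 0.302, identical to the unadjusted change contrast. That check used two waves and no participant slopes.

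The site differences here were made large to expose the mechanism; they are not an estimate for this trial. The same logic applies to the fixed covariates. They are listed without time interactions, so they adjust level and not differential change.

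**Step 3. Size for one omitted variable.** Bias ≈ b × SMD, where SMD is the imbalance between arms and b the effect on change in SD per SD. Both are assumptions; only 0.27 and 0.50 come from the Power section.

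| SMD | b=0.1 | b=0.2 | b=0.3 |
|---|---|---|---|
| 0.1 | 0.01 | 0.02 | 0.03 |
| 0.2 | 0.02 | 0.04 | 0.06 |
| 0.3 | 0.03 | 0.06 | 0.09 |
| 0.5 | 0.05 | 0.10 | 0.15 |

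The range is 0.01-0.15 SD. Against g=0.27 this is 0.01/0.27 = 4% to 0.15/0.27 = 56%. Against d=0.50 it is 2% to 30%. As a check, a simulation with a 0.3 SD symptom imbalance and b=-0.2 (expected -0.06) gave -0.05, and -0.01 after adjustment.

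**The case against.** The strongest reply is that the plan does more than its matching list suggests. Site is in the outcome model. The pre score is a level of the outcome, so time-by-treatment already removes baseline level differences in the objective tests. Self-reported cognition and biases are matched, and these are plausible drivers of a choice made in conversation about personal goals. Measures introduces its list as examples, and an unseen analysis plan may add to it. The limitation statement promises control of measurable characteristics only. All of this stands. It rules out saying that site and objective baselines are unadjusted, or that the list is closed everywhere. It does not supply the five variables missing from both the list in Data Analysis, which is stated without qualification, and the model.

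A reader might infer a larger bias through regression to the mean. With an imbalance of 0.3-0.5 SD and a test-retest correlation of 0.5-0.7, (1-r)×SMD runs from 0.3×0.3 = 0.09 to 0.5×0.5 = 0.25 SD, or 33-93% of 0.27. That requires choice to act on the observed test score. Nothing says participants or coordinators see test results when choosing. If choice follows stable traits or preference, this component can be about zero.

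A reader might also infer that sequential sites have no concurrent control. The documents do not go so far. The Abstract has every site running both interventions annually, and Results reports that all sites have run both. Sequence may mean alternating cohorts in the same period.

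Finally, exact matching on site and period could be costly: 390/5 = 78 recruits per site, and 78×0.7 ≈ 55 after the planned 30% attrition, both arms together. Matching on noisy baseline outcome scores can itself induce regression to the mean. Both objections stand and shape the remedy.

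**Conclusion.** The point holds in a bounded form. Allocation is by preference, and baseline symptoms, diagnosis, motivation, concurrent therapy and enrolment period are named in neither the matching list in Data Analysis nor the outcome model. Site and objective baseline tests are handled in part: differences in level are dealt with, but site differences in change and change that depends on baseline are not.

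The size cannot be derived from the documents. The 0.01-0.15 SD range (4-56% of g=0.27) is for one omitted variable and rests on the assumed imbalance and effect on change. The low end is negligible; the high end would seriously distort the smaller primary effect. The direction is not known. The descriptions of the design as concurrent and of delivery in sequence need reconciling, but they do not show that any site lacks a contemporaneous comparison.

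**What to change.** 1. Add to the propensity score: baseline PANSS-6, BNSS and PSYRATS, diagnosis group, baseline motivation for intervention, concurrent therapy at entry, site and enrolment period. Use motivation only if it is recorded before the choice is made, which the article does not say.
2. In the outcome model, include site-by-time and enrolment-period-by-time terms, and time interactions for any covariate still unbalanced after matching. Main effects alone would leave the contrast of interest largely unchanged.
3. Add a sensitivity analysis that adjusts follow-up scores for the baseline objective test, and one limited to sites offering both interventions at the same time.
4. Reconcile Study Design with Cognitive Health Interventions: state which sites deliver in sequence and in what sense the control there is concurrent.

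The cost is somewhat fewer close matches and a slightly larger model. Putting site and period in the score, and not matching on them exactly, limits the loss. No new data collection is needed. With 114 of 390 recruited as of winter 2024, the covariate set should be fixed before outcomes are analysed, since choosing it afterwards would invite bias of its own.

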### Measures

To assess the effectiveness of the 2 digital cognitive health interventions (objective 1), primary outcomes will encompass quantitative measures of cognitive function for ABCR and cognitive biases for MCT. These outcomes were selected in alignment with the primary targets for each intervention and primary outcomes assessed in the past ABCR and MCT studies. To capture the full extent of these outcomes, both objective and self-report measures were selected. The collection of these primary outcomes will be prioritized. Secondary outcomes for both interventions will include clinical and functional measures. Propensity score matching will consider background characteristics such as sociodemographic variables, illness duration, medication dosage, length and nature of prior treatment, and subjective reports of cognitive capacity and biases. To promote data quality, research staff will partake in centralized interrater reliability sessions every 6 months. To evaluate the implementation strategy (objective 2), a combination of quantitative and qualitative data will be gathered. Refer to Table 1 for a breakdown of the data types to be collected, organized by objectives, time points, and stakeholders.

**Table 1 table1:** Summary of the type of data to be collected as a function of objectives, time points, and stakeholders.

Objectives or data type and measures			Measurement time points		Stakeholder groups

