**1. Effectiveness (quantitative)**					
	Cognitive tests or tasks: Brief version of the CANTAB^a^ computerized battery (Intra-Extra Dimensional Set Shift, Stocking of Cambridge, and Spatial Working Memory)^b^ [42] Wechsler Memory Scale (Logical Memory Subscale)^b^ [43] Cognitive bias against disconfirmatory evidence story^b^ [44] Jumping to conclusions (Beads)^b^ [45] Subjective cognition: Subjective Scale to Investigate Cognition in Schizophrenia (Brief)^b^ [46] Cognitive Motivation Scaleb [47] Davos Assessment of Cognitive Biases Scale^b^ [48] Symptoms: Positive and Negative Syndrome Scale-6 [49] Brief Negative Symptom Scale [50] Psychotic Symptom Rating Scales [51] Psychosocial: Self-Esteem Rating Scale—Short Form [52] Overall Emotional and Social Loneliness Scale [53] Short Warwick-Edinburg Mental Well-Being Scale [54] Questionnaire About the Process of Recovery [55] Basic Psychological Need Satisfaction and Frustration Scale [56] Autonomous-Controlled Motivation for Intervention Questionnaire [57] Personal and Social Performance [58]	Preintervention Postintervention 3-month follow-up		Service users	
	Intervention: Health Care Climate Questionnaire [59] Autonomous-Controlled Motivation for Intervention Questionnaire [57] MMI^c^ Cognitive Training Questionnaire [60] Satisfaction With Therapy (STQ^d^) [61] Time spent on cognitive drill exercises (ABCR^e^) Last log in (iCog platform)	Midintervention		Service users	

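### Matching the self-chosen arms on the baseline of two self-report primary scales, then testing change from that same baseline, can mask each therapy's effect through regression to the mean

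*Protocol article*

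**What the plan says.** All references are to the protocol article.

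- **Matching set.** Measures lists among the matching variables "length and nature of prior treatment, and subjective reports of cognitive capacity and biases". Data Analysis repeats this, naming "subjective reports of cognitive capacity and cognitive biases", and treats these reports as background variables.
- **Primary outcomes.** Table 1 flags as primary both "Subjective Scale to Investigate Cognition in Schizophrenia (Brief)^b" and "Davos Assessment of Cognitive Biases Scale^b^ [48", measured before the intervention, after it and at three months.
- **Model.** Data Analysis states: "Factors of interest will include fixed time (pre, post, and follow-up), fixed treatment (ABCR and MCT), fixed time and treatment interaction (time*treatment". The baseline score is therefore part of the response. The fixed covariates do not include the self-report baselines.
- **Allocation.** Under Cognitive Health Interventions, participant and coordinator talk through both options and "they will collaboratively determine which intervention best aligns with the participant"'s goals and preferences.
- **Bias.** Data Analysis says that running the procedure twice, with the roles swapped, brings in no bias, because nobody is counted more than once within a comparison. Regression to the mean is not discussed.

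**The concern.** A single baseline score holds a stable part and a part particular to that day. Suppose people with more everyday cognitive complaints tend to choose ABCR. To match them, the procedure must take MCT participants whose complaints that day were high for their arm, and ABCR participants whose complaints were low for theirs. By the post visit each group drifts back toward its own arm's level. Because the matching score is also the starting point of change, the drift enters time*treatment.

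The likely direction matters. The matched MCT controls appear to improve on cognitive complaints without any treatment effect, which hides an ABCR benefit. On the Davos scale the mirror image hides an MCT benefit. What is at stake is a real effect on a primary self-report outcome that is shrunk, missed or shown with the wrong sign.

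**Working it through.** **Inputs from the article.** Anticipated primary effects are d = 0.50 (CR) and g = 0.27 (MCT), and the planned total is 390 (Power section). The plan gives no figure for this bias. Its 390 reproduces as 300 x 1.30 and is used here only to size simulations; 390 x 0.70 = 273, or about 137 per arm after the stated attrition.

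**Assumed inputs.** Test-retest reliability rho and the stable arm difference Delta (in SD) are not in the article and are shown as ranges.

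**Formula.** Take higher scores as worse and no treatment effect. In an arm with stable mean mu, a person with baseline y has expected post score mu + rho(y - mu), so expected change is (1 - rho)(mu - y). For two people matched at the same y in different arms, the difference in change is

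(1 - rho)(mu1 - mu2) = (1 - rho) x Delta.

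Swapping which arm is called the control changes only the sign convention, so running the procedure twice does not reveal the bias.

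**Results when the arms differ in stable level, no treatment effect.** Each cell gives the formula value, then in brackets the simulated bias and the share of trials significant at 5%. Simulation: 390 people, logistic propensity score on the scale plus one other covariate, 1:1 caliper matching, post-minus-pre contrast, 800 runs per cell.

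| Delta | rho 0.6 | rho 0.7 | rho 0.8 |
|---|---|---|---|
| 0.2 SD | 0.08 (0.077; 11%) | 0.06 (0.061; 10%) | 0.04 (0.044; 8%) |
| 0.3 SD | 0.12 (0.122; 23%) | 0.09 (0.090; 16%) | 0.06 (0.059; 12%) |
| 0.5 SD | 0.20 (0.200; 51%) | 0.15 (0.151; 41%) | 0.10 (0.099; 27%) |

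With 137 per arm and Delta = 0.5, the significant shares are 38%, 27% and 18%. With Delta = 0 the bias is nil. Without the scale in the match, the change contrast has a bias of about 0 and about 5% significant results.

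**Direction.** In null runs at Delta = 0.5, essentially none of the significant results favoured the therapy whose target the scale measures.

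**Effect on a true benefit.** At Delta = 0.5 and rho = 0.7 the bias is 0.30 x 0.5 = 0.15 SD. A true MCT effect of 0.27 becomes 0.27 - 0.15 = 0.12 SD, a loss of 0.15/0.27 = 56%. Simulation with 137 per arm also gave 0.12 SD, significant in 21% of trials. For d = 0.50 the loss is 0.15/0.50 = 30%.

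**Baseline as a covariate after matching.** This does not help: the bias at Delta = 0.5 and rho = 0.7 is still 0.153 SD.

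**The opposite selection model.** If choice depends only on the score observed that day (log-odds 0.5 per SD), the matched contrast has a bias of about 0. The contrast without matching is then biased by -0.189, -0.139 and -0.094 SD at rho 0.6, 0.7 and 0.8.

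**The case against.** The strongest reply is that the plan's choice is defensible. Participants choose in a meeting at entry, perhaps guided by how they feel then, and in that case matching on the current score is right and leaving it out does harm. The article does not establish which selection model holds. This stands, and it is why the scales should not simply be dropped from the score.

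The size also rests on assumptions. At a difference of 0.2 SD the bias is only 0.04 to 0.08 SD. The planned score includes other variables. If half of a 0.5 SD difference runs through them, the bias at reliability 0.7 falls to 0.10 SD with 12% significant; if they predict the score but not the difference, it rises to 0.19 SD. None of the calculations fits the full three-time-point mixed model. The article does not name the instruments in the score, so their identity is inferred. They are, however, the only listed self-reports of capacity and of bias; the Cognitive Motivation Scale is also flagged primary but measures motivation.

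Three stronger readings are tempting and not supported:

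- A reader might take the raised rejection rates as false claims of benefit. In the likely direction they run against the therapy on its own target.
- A reader might conclude that self-report and objective primaries cannot be read together. No bias was calculated for the objective tasks, so this is not shown.
- A reader might ask for significance in both analyses before claiming an effect. That leaves the masking in place. In two sets of simulations at a 0.5 SD difference, reliability 0.7 and a true effect of 0.27 SD, such a rule detected the effect in 12% and 24% of trials, against 76% and 82% for the analysis without the scale in the score.

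**Conclusion.** The concern holds as a conditional risk. The double use of the baseline is in the text, subject to the inference about which instruments are meant. The bias needs arms that differ in stable level and a scale with imperfect reliability. Choice by personal goals makes the first plausible but gives it no size. Over the assumed ranges the bias is 0.04 to 0.20 SD, most likely against each therapy on its own target, so the harm is a masked or wrong-direction effect rather than a spurious benefit. It disappears if choice follows the momentary score. The article's reason for saying that the repeated procedure brings in no bias, single counting, does not bear on this mechanism. Control of measured background characteristics, offered in Strengths and Limitations, does not settle it either, since the problem arises from matching on a noisy measure of the outcome itself.

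**What to change.** For each of the two scales, prespecify a sensitivity analysis that repeats the matching and the model with that scale's own baseline left out of the propensity score and all other variables kept. Report both estimates with confidence intervals, labelled by the assumption each rests on: choice on the momentary score (baseline in the score) and choice on a stable level (baseline left out). Interpret the scale cautiously if the two differ materially, and do not make significance in both a condition for claiming an effect. Qualify the Data Analysis statement about bias so that it covers only the double counting of participants.

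The cost is one extra matching and model fit per scale and a few sentences in the analysis section, plus a less clear-cut conclusion if the two results disagree.

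### Repeating the propensity score matching with the arms' roles swapped does not validate the matching, as the protocol says it does

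*Protocol article*

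**What the plan says.** In the protocol article, under Data Analysis, matching is used to "identify a subset of participants who will comprise the active control group that is equivalent to the intervention group" on background variables. A mixed model then compares the groups. The whole procedure is carried out twice, first with ABCR as the intervention and MCT as control, then the reverse.

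Three claims are made for the repetition:
- on double counting: "This approach ensures that participants are not counted twice and is an integral part of the propensity score matching procedure";
- on validation: "Statistically, performing the procedure twice helps to validate the robustness of the matching process without introducing bias";
- as the reason: "each participant is only included once in each comparison".

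The outcomes are not divided between the two runs: "Primary and secondary outcomes will be compared between the 2 interventions, using one as the active control for the other". Under Measures, each intervention does have its own primary domain: "primary outcomes will encompass quantitative measures of cognitive function for ABCR and cognitive biases for MCT". Under Cognitive Health Interventions, participants and the site coordinator choose the intervention together, according to goals and preferences. No arm sizes, matching ratio or caliper are given.

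**The concern.** A check on matching has to be able to fail when the matching is poor. Swapping the labels of two arms turns ABCR minus MCT into MCT minus ABCR. It does not examine covariate balance, sensitivity to the ratio or caliper, or confounding by preference, which is the central threat when people choose their treatment. Using each person once within a comparison does not stop that person from appearing in both comparisons, so the two results are not independent.

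At stake is what the trial can claim. Two results that must largely agree would be offered as evidence that the matching worked. A secondary matter is that matching may discard participants, depending on its settings, and the sample size shows no allowance for that.

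**Working it through.** **Step 1. Set the two runs side by side.** By the Data Analysis section, the arms, matching variables, mixed model and outcomes are the same in both runs. Only the arm from which the matched subset is drawn changes. The two arms cannot each be larger than the other, so in at least one run the control pool is no larger than the group it must match.

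**Step 2. How far do the runs repeat each other?** The article gives no settings, so these are assumptions: 300 analysed participants, 1:1 greedy nearest-neighbour matching without replacement, and a single matching score with SD 1 in each arm. The arms differ by 0.3 or 0.5 SD on that score. The outcome is 0.4 × score plus noise of SD 0.9, with no treatment effect. There were 200 simulated trials per setting. Overlap is the number of people in both matched samples divided by the number in either. The correlation is between ABCR minus MCT from run 1 and MCT minus ABCR from run 2.

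| Arm split | Caliper | Overlap | Correlation | Discarded per run (of 300) |
|---|---|---|---|---|
| 150/150 | none | 100% | -1.00 | 0 |
| 150/150 | 0.2 | 77–81% | -0.90 to -0.91 | 49–67 |
| 165/135 | none or 0.2 | 75–83% | -0.87 to -0.93 | 30–73 |
| 180/120 | none or 0.2 | 72–73% | -0.79 to -0.86 | 60–85 |
| 200/100 | none or 0.2 | 60–65% | -0.71 to -0.78 | 100–112 |

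With equal arms and no caliper, 1:1 matching returns everyone. Group means on every covariate are what they were before matching, so the matching balances nothing, and run 2 is run 1 with the sign changed.

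**Step 3. False-positive rate.** Take two two-sided 5% tests per outcome whose statistics are bivariate normal with correlation r. The chance of at least one rejection under no effect is 1 − P(|Z1| < 1.96 and |Z2| < 1.96).
- |r| = 1.00: 5.0%
- |r| = 0.90: 7.0%
- |r| = 0.88: 7.2%
- |r| = 0.71: 8.3%

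Two independent tests would give 1 − 0.95² = 9.75%.

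**Step 4. Allowance for discarded participants.** The Power section requires 300, adjusts for 30% attrition and, taking the propensity score into account, arrives at 390. That figure is reproduced by 300 × 1.30 = 390. After 30% attrition, 390 × 0.70 = 273 remain, which is already 27 below 300 before any matching loss. Dividing by the retained fraction would give 300 / 0.70 = 429. The attrition multiplier alone accounts for the whole of 390, so no allowance for matching is visible.

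The stated power of up to 90% comes from a Monte Carlo model that is not described, so it cannot be reproduced. For orientation only, a simple two-group comparison (1:1, two-sided 5%, SD 1) has power Φ(d√N/2 − 1.96). For the MCT effect of 0.27:
- N = 300: Φ(2.338 − 1.96) = 64.7%
- N = 273: 60.7%
- N = 240: 55.2%
- N = 200: 48.0%

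The last two are assumed sizes after matching. They are losses of 33/273 = 12% and 73/273 = 27%, inside the 10% (30/300) to 37% (112/300) simulated in step 2 for settings that discard anyone.

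**The case against.** The strongest reply is that two runs are not in themselves a mistake. Matching MCT participants to ABCR participants estimates the effect in people who chose ABCR; the reverse estimates it in people who chose MCT. These can be legitimate separate questions, and the arm-specific primary domains under Measures fit such a structure. This stands. However, the article gives validation as its reason, and it compares all outcomes in both runs.

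It is also fair to say that arm sizes, ratio and caliper may be set out in a fuller plan, and that preference-based choice could make the arms unequal. This also stands. A reader might infer that the arms are of similar size, that the second run uses nearly the same people, and that participants are bound to be lost. The documents do not support that combination. Both interventions are offered at every site, but no ratio is stated. Equal arms without a caliper lose nobody, while the settings that lose people reduce overlap, to about 60% at 2:1. The criticism survives at that extreme, because a correlation of -0.71 is still not independent evidence.

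Finally, the model adjusts for age, illness duration, medication dosage and prior psychological treatment and includes the baseline time point. If the matching balances nothing, some adjustment therefore remains. That softens the consequence but does not make the swapped run a test of the matching.

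**Conclusion.** The validation claim is wrong as written, whatever the matching settings. The two runs are strongly dependent: overlap of about 60% to 100% and correlation of about -0.7 to -1.0 for arm splits from 1:1 to 2:1. Those figures rest on assumed 1:1 nearest-neighbour matching without replacement. The no-replacement part is consistent with the article's statement that each person is used once per comparison; the rest is not stated.

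A reader might infer a serious multiplicity problem. The figures do not support that: where the runs differ, the rate per outcome is about 7% to 8% in place of 5%, and for exact mirror images it stays at 5%. Nor is a loss of power established. Loss depends on a caliper or unequal arms, and all that can be said is that 390 leaves 273 after attrition, with no visible allowance for matching. The main harm is interpretive: agreement between near mirror images would be taken as a robustness check.

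**What to change.** 1. Delete the sentence claiming validation, and the claim that running twice prevents double counting.
2. Name one primary ABCR-minus-MCT contrast for each primary outcome. It can come from a single analysis that keeps all first-course participants, for example with overlap weights or full matching, or from one named matching direction. Weighting is a suitable option and not the only correct method.
3. If both directions are kept, label them as effects in ABCR choosers and in MCT choosers, and state that the second does not count as confirmation of the first.
4. Judge the matching or weighting by standardised mean differences on the matching variables afterwards.

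The cost is a change of wording in the analysis plan and, if weighting or full matching is chosen, a different option in the same R workflow. The downside of weighting is that the weighted population has to be described. No data collection changes.
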